### 2.10. Ethical Aspects

The study obtained ethical approval from the Liguria Reginal Ethics Committee (Ref. number 602/2023, ID 13601). If the participating healthcare institutions need the approval of their respective local ethic committees, the required documentation will be provided.

Data will be processed in accordance with the General Data Protection Regulation (GDPR) [23]. Each institution will provide data for the purposes of the study, using an alphanumeric code that will not allow the research team to identify any participants. All data available from nursing records will be retrospectively extracted from the EHR for only those patients who meet the inclusion criteria. The local investigator of each included hospital will upload the database of extracted data into a specific cloud (with the necessary security measures), located on a server maintained and managed by The Centre of Excellence for Nursing Research and Development (CERSI-FNOPI), the promoter of this study. Only the CERSI-FNOPI research team will have access to uploaded data. The local investigators will be provided with a password that will give them access to their personal folders where the database can be uploaded. Moreover, the local investigators will have access only to their own folders, with the opportunity to modify the uploaded database if necessary. No local investigator will be able to access the data uploaded by the other local investigators. The study will be conducted in conformity with the principles of the Helsinki Declaration, the current norms of good practice, and local laws to ensure the maximum protection of the subjects involved. The data collection form will be password-protected. Data will be kept in an anonymous database. CERSI-FNOPI will store all anonymized data for five years.

## 3. Limitations

The limitations of the study may be related to the number of missing data from nursing records, as the data will be collected from hospitals with different nursing record systems. This could lead to sampling bias. However, appropriate handling of missing data (e.g., multiple imputation) will be considered to reduce this bias. Another limitation could be related to the choice of including a limited number of acute care wards of five hospitals in this study, without adjusting for differences in hospital size. This may limit the representativeness of the findings, as the results may not fully reflect the broader population of Italian Hospitals. However, the inclusion criteria were carefully assessed to guarantee both the feasibility of this study and the generalizability of the results. Moreover, it should be considered that this will be the first descriptive study that will present a picture of existing differences in nursing costs between different DRGs and within the same DRGs. Finally, the study’s cross-sectional design, which focuses on patients admitted and discharged during 2022, represents another limitation.

## 4. Dissemination

CERSI-FNOPI will distribute the results of this study. The results of this study will be presented at conferences as abstracts, posters, and oral presentations, and published in peer-reviewed scientific journals. The results will also be reported by CERSI-FNOPI to national and local government authorities, policy-makers, and stakeholders. Finally, the study results will be shared with participating facilities.

## Figures and Tables

**Figure 1 healthcare-13-00167-f001:**
[figure not shown]
Study phases.

**Table 1 healthcare-13-00167-t001:** Variables that will be collected divided by data source.

Hospital discharge data	Patient sociodemographic characteristics
	Date of patient admission
	Date of patient discharge
	DRG^†^ number assigned for each admission
	MDC number related to assigned DRG
	Admission diagnosis ^$^
	Discharge diagnosis ^$^
	1st secondary diagnosis ^$^
	CIRS
Nursing record data	Number of nursing activities performed for the same DRG
	Type of nursing activities
	Patient-related care complexity *
	Nursing assessment ^§^

DRG^†^: Diagnosis-Related Group; MDC: Major Diagnostic Category; ^$^: based on the *International Classification of Diseases*, 9th Revision, Clinical Modification (ICD-9-CM); CIRS: Cumulative Illness Rating Scale; ^§^: intended as the assessment carried out on the patient through the use of rating scales according to the company organization; *: care complexity will be measured by means of a validated tool used by hospitals.

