## Abstract

**Background**: Rising costs and demands for improved quality of care present complex challenges for existing healthcare systems. The strain on healthcare resources is exacerbated by the increasing complexity of patient conditions. The Diagnosis-Related Group (DRG) system classifies inpatients according to clinical and treatment criteria, controls healthcare expenditures, and ensures the sustainability of procedures. The cost of nursing care is included in the DRG system in the same way as other fixed costs of hospital care, but the amount of nursing care provided for the same DRG can vary widely. This study, which is based on this protocol, will aim to assess the variability of nursing costs within and across DRGs and to measure how much variability in nursing care is explained by DRGs by comparing nursing care delivery in acute care hospitals with the DRG reimbursement system in Italy. It is necessary to develop a specific protocol to ensure systematic and consistent data collection at the national level. **Methods**: A multicenter retrospective cross-sectional study will be conducted. A random sample of five public Italian hospitals will be enrolled. Patients included in medical or surgical DRGs, hospitalized and discharged in 2022 will be included. Data will be collected retrospectively from two sources: hospital discharge records and nursing records. Inferential statistics will be used to assess the variability of nursing time and costs across hospitals and DRGs. Nursing costs will be determined by several factors, including time spent on nursing activities and the hourly wages of nursing staff. The time needed to complete each activity will be estimated by a convenience sample of nurses from the hospitals included in this study. The annual salary of nurses will be used to calculate the nursing cost per minute, multipled by the amount of time spent per each nursing activity. The cost per patient per day of hospitalization will be calculated. **Conclusions**: The results of this study will shed light on the variation in nursing care across different DRGs. This understanding will guide recommendations for optimizing healthcare resource allocation and enhancing the efficiency of the DRG system in Italy.

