In Italy, there are currently no studies that have shown whether the inclusion of nursing data in the reimbursement systems of healthcare services can contribute to a more equitable distribution of healthcare financial resources. The study based on this protocol will aim to fill this gap by examining the costs related to nursing activities within the DRG reimbursement system. The findings could clarify the variability in nursing costs provided within the same DRG, offering insights on how to better align DRG reimbursements with actual nursing care costs. Achieving this alignment may involve adjusting the DRG cost weights to account for nursing care or establishing a separate nursing intensity weight for each DRG category. Moreover, the results could help develop a replicable framework in this and other settings for assessing nursing costs and quality of care and further examine the relationship between care, patient outcomes, and healthcare costs.

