## 2. Materials and Methods

### 2.1. Aims

The primary aims of this study are (1) to assess the variability of nursing costs between different DRGs and within the same DRG; and (2) to measure how much variability in the intensity of nursing care is explained by DRGs.

The secondary objectives of this study are (1) to measure the amount of nursing activity in acute care hospitals; (2) to examine the variability of the intensity of nursing care activities by DRG within patients and across patients controlling for hospital and region; and (3) to identify and quantify any differences in care needs among patients discharged with the same DRG.

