### 2.8. Data Analysis

Descriptive statistics (frequency, percentage, mean, median, range, and standard deviation) will be used to describe the sample. *t*-tests, ANOVA (or related nonparametric tests in case of a non-normal distribution of dependent variables), linear regression, and quantile regression will be performed to evaluate the possible variability in nursing time across hospitals and DRGs.

The chi-square test will be used to analyze any differences in the average frequency of nursing activities within the same DRG. In addition, we will perform linear, logistic and quantile regression, considering cost as the outcome of nursing care. Nursing costs will be assessed across hospitals and DRGs. The quantile regression will be used to explore which factors are associated with the different quantiles of nursing costs.

Nursing costs will be calculated based on several factors, including the average time required to perform each procedure, nurses’ hourly wage, the cost of materials used, and the average length of patient stay. Nursing time will be estimated using a convenience sample of nurses from the hospitals included in this study. For each nursing activity, the participating nurses will indicate the average time spent on the activity and devices relevant to each intervention. Nursing costs will be calculated by applying nurses’ salaries, based on national cost tables for nursing professionals. The annual nursing salary will be used to estimate the cost per minute of nursing time. This cost per minute will then be multiplied by the amount of time spent on each nursing activity and by the total number of activities performed for each patient. Additionally, the cost of devices required to perform each activity will be included, based on prices from the national price list. Thus, the cost per patient per day of hospitalization will be calculated. This cost will enable us to compare patients with different lengths of stay. Finally, subgroups based on patient complexity will be considered.

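### The promised comparison with DRG reimbursement has no weight or tariff source and no analysis, and the only final cost unit is per day although the DRG is assigned per admission

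*Protocol article*

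**What the plan says.** The Abstract presents a comparison with payment as the means by which the study will work: "by comparing nursing care delivery in acute care hospitals with the DRG reimbursement system in Italy". The Introduction, in conditional wording, expects the findings to help by "offering insights on how to better align DRG reimbursements with actual nursing care costs", and one route it names is "adjusting the DRG cost weights to account for nursing care". Section 2.8 closes its case-mix paragraph by saying that the results will support treating nursing separately within the Italian prospective payment system.

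The formal primary aims in Section 2.1 are narrower. The first is "to assess the variability of nursing costs between different DRGs and within the same DRG"; the second is "to measure how much variability in the intensity of nursing care is explained by DRGs". Neither mentions a weight, a tariff or an amount paid.

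Table 1 lists a DRG number for each admission and the "MDC number related to assigned DRG". It also lists admission and discharge dates, and Section 2.2 says length of stay is extracted. It lists no relative weight, tariff or reimbursed amount.

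Section 2.8 builds cost from nursing minutes priced by salary, multiplied by the number of activities for the patient, plus devices. It then states: "Thus, the cost per patient per day of hospitalization will be calculated". The reason given is comparability between patients whose stays differ in length. Section 2.8 names national sources for salaries and device prices, but none for DRG weights or payments, and no listed analysis sets nursing cost against either.

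**The concern.** Two parts of the plan do not meet its stated purpose.

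The first is the comparator. A comparison with a reimbursement system needs something from that system beyond the group label: a weight, a tariff or a payment. Without one, the analysis describes nursing cost by DRG code. It does not show whether more highly weighted DRGs use more nursing, or how nursing cost relates to what is paid.

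The second is the unit. The Introduction states the premise under examination, that patients in one group should use similar resources. The group is assigned once per admission, so that premise concerns the whole stay. Dividing each patient's cost by days in hospital takes out the part of the spread that comes from staying longer or shorter. Eligibility in Section 2.5 sets only a lower limit on stay (more than one day), so length of stay can vary widely within a DRG. This reaches primary aim 1, which concerns cost variability within the same DRG, as well as the payment conclusions.

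**Working it through.** The plan gives no figure to reproduce. The check has three steps.

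**1. Purpose against data and analysis**

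| Stated purpose | What it needs | What the article provides |
|---|---|---|
| Cost variability between and within DRGs (aim 1) | Nursing cost, DRG label | Both; final cost unit is per day |
| Share of nursing-intensity variability explained by DRGs (aim 2) | Nursing intensity, DRG label | Both |
| Comparison with DRG reimbursement (Abstract) | Weight, tariff or payment, and an analysis using it | DRG and MDC numbers; no source and no analysis |

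**2. Units**

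The relation is cost per stay = cost per day × length of stay. Take two patients in one DRG with the same daily cost *c*, and stays of 3 and 9 days (assumed values).

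- Per day: *c* and *c*, ratio 1.0.
- Per stay: 3*c* and 9*c*, ratio 9/3 = 3.0.

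The per-day figure shows no variation where the admission-level figure shows a threefold difference. The same holds between two DRGs with mean stays of 3 and 9 days.

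**3. Possible size within a DRG (illustration only)**

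The documents give no coefficient of variation (CV), so all of these are assumed. If daily cost and stay are independent,

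CV²(stay cost) = (1 + CV²(day cost)) × (1 + CV²(length of stay)) − 1.

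With a per-day CV of 0.20, the squared per-day CV is 0.04.

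| Length-of-stay CV | CV² of stay cost | Per-day CV² as a share |
|---|---|---|
| 0.4 | 1.04 × 1.16 − 1 = 0.206 | 0.04 / 0.206 = 19% |
| 0.7 | 1.04 × 1.49 − 1 = 0.550 | 0.04 / 0.550 = 7% |
| 1.0 | 1.04 × 2.00 − 1 = 1.080 | 0.04 / 1.080 = 4% |

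The result depends heavily on the per-day CV. Doubling it to 0.40 (squared 0.16) gives:

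- length-of-stay CV 0.4: 0.16 / (1.16 × 1.16 − 1) = 0.16 / 0.346 = 46%;
- length-of-stay CV 0.7: 0.16 / (1.16 × 1.49 − 1) = 0.16 / 0.728 = 22%;
- length-of-stay CV 1.0: 0.16 / (1.16 × 2.00 − 1) = 0.16 / 1.32 = 12%.

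Independence matters too. If daily cost falls as stay lengthens, the gap narrows and can reverse. In the extreme case of equal total cost over 3 and 9 days, the per-stay ratio is 1.0 and the per-day ratio is 3.0. The two units answer different questions, and the direction of the difference has to be measured.

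**The case against.** The strongest case on the other side has four parts.

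- **Per-stay cost is already within reach.** Section 2.8 computes a total over all of a patient's activities before the per-day figure, and length of stay is collected. The regressions are described only as having cost as the outcome, so nothing restricts them to the per-day version. This stands: the information is not lost, and the percentages above do not measure something the study can never recover. It does not change the fact that per day is the only final unit the article specifies.
- **Table 1 is not a list of reference tables.** It covers discharge and nursing records. The salary tables and device price list are not in it either, and a weight or tariff could be attached through the DRG number. This also stands, assuming that a published table exists, which the article neither names nor excludes. However, Section 2.8 does identify the salary and device-price sources and says how they are used. For DRG payment it gives neither a source nor an analysis.
- **The formal aims need only the DRG label, and the per-day unit has a stated reason.** Correct. A per-day measure is also a natural choice for the nursing intensity in aim 2. For aim 1, though, the label alone does not settle which unit the within-DRG spread refers to.
- **The Abstract may mean the DRG as a classification, not as a payment.** This reading is possible, since the sentence concerns variability explained by DRGs, and the Introduction's wording on alignment is conditional. If that is the intention, the reimbursement wording in the Abstract, Introduction and Section 2.8 goes further than the plan and should be narrowed.

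A reader might infer that the comparison cannot be made, or that the primary aims are blocked. The first two parts rule out the former and the third rules out the latter.

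**Conclusion.** The point holds as a mismatch between stated purpose and stated plan. The Abstract promises a comparison with DRG reimbursement, and Section 2.8 seeks evidence for the payment system, yet the article names no weight or tariff source and no analysis against one. Its only final cost unit is per day, while the DRG is assigned per admission.

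Followed as written, a per-day comparison would leave length-of-stay variation out of the within-DRG spread that aim 1 and the payment conclusions concern. The threefold example follows directly from the units, given equal daily cost. The 19% to 4% range is only an illustration: it assumes a per-day CV of 0.20, length-of-stay CVs of 0.4 to 1.0, and independence of daily cost and stay. It is not an estimate for this study.

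No data collection needs to be repeated, and neither primary aim is invalid. A specific improvement is available at little cost and should be made before the analysis.

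**What to change.** 1. In Section 2.8, state that nursing cost will be reported and modelled **per stay as well as per day** for the between-DRG and within-DRG variability in primary aim 1. Keep the per-day figure for its stated purpose.
2. Then do one of the following:
   - **Link and analyse.** Name the source of the DRG weight or tariff applicable to the 2022 admissions, attach it through the DRG number, and add an analysis of per-stay nursing cost against it. Useful outputs are the variance explained by weight compared with that explained by DRG category, and nursing cost as a share of tariff with its within-DRG spread.
   - **Narrow the wording.** Limit the reimbursement statements in the Abstract, the Introduction and the case-mix paragraph of Section 2.8 to the aims in Section 2.1.

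The first option costs one look-up merge on a variable already collected and a little more analysis, with no new patient data, provided that a usable weight or tariff table exists. The second is an edit to the text. Step 1 is worthwhile under either option, because aim 1 concerns cost within a group that is assigned per admission.

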## Data Availability

No new data were created or analyzed in this study. Data sharing is not applicable to this article.
